## **E7 *Economic Assessments***

Resource-use data to be collected on the study case report form (CRF) will include hospitalizations, emergency department visits, selected cardiac procedures, and tests. Hospital bills (detailed, summary ledger, and UB 04) will be collected by the EQOL CC at the DCRI for all hospitalizations identified throughout the length of the study. They will include care at clinical sites and at institutions not participating in PROMISE. In addition, cost-to-charge ratios will be obtained from each hospital where a PROMISE follow-up hospitalization is reported.

## **E8 *PROMISE Biorepositories***

### **8.a *Imaging and Electrocardiograms***

Since future developments in image interpretation and integration with clinical data will remain important in the diagnosis and management of chronic diseases of CAD, PROMISE will create a unique anonymized “Image and ECG Data Warehouse” with all initial noninvasive test images, stress ECGs, and initial catheterization films, which will be linked to clinical information. Collection and release of data and images will be at the discretion of the study team including NHLBI and is included as part of the subjects’ initial consent.

### **8.b *Blood Biomarkers and Genomics***

The PROMISE investigators also believe that an integrated approach to disease characterization and therapeutic responses will play an increasingly important role in the diagnosis and management of chronic diseases such as CAD. Accordingly, subjects will be asked to provide a blood sample for deposit into a biomarker repository at the time of randomization for future assessment of advanced molecular biomarkers (plasma, serum) such as troponin and high-sensitivity C-reactive protein relevant to disease characterization, risk stratification, characterization of treatment response, and adverse effects. In addition, subjects will be requested to separately consent to allow use of the biorepository sample for genetic testing (DNA).

|                                           |
|-------------------------------------------|
| <h2>F Statistical Plan</h2> |
|-------------------------------------------|

### **F1 *Sample Size Determination and Statistical Power***

Several design factors and research objectives were considered in selecting the target sample size for the study. First, the number of subjects was determined so there would be a sufficient number of endpoints to provide a high degree of power (greater than or equal to 90%) for testing the primary superiority hypothesis. Second, the statistical power for secondary endpoints was considered, including the composite clinical endpoints and the economic and QOL endpoints. Third, it was considered important for the sample size to be large enough to permit a prudent examination of diagnostic testing effects in selected subgroups of subjects where anatomic testing might be particularly advantageous or where the question of a benefit from CTA is particularly relevant.

Important prespecified subgroups of interest in this study include those defined by age, sex, race, comorbidity, cardiovascular risk factors, the prerandomization choice of functional test, and characteristics of the precipitating symptoms. Fourth, the sample size was selected to provide a reasonable level of confidence for detecting clinically important outcome differences between the anatomic and functional testing strategies even if current projections of event rates and the hypothesized differences in clinical outcomes between the 2 arms prove to be optimistic. A fifth consideration was the adequacy of the sample size for assessing noninferiority of anatomic testing compared with functional testing in the event that the anatomic testing strategy is not demonstrated to be statistically superior to functional testing. Finally, although the study objectives are expressed in terms of testing specific hypotheses (i.e., that the anatomic testing strategy is superior [and if not superior, then noninferior]) to functional testing, another important objective of the trial is to estimate the magnitude of the difference in outcomes to within an acceptable level of statistical precision, regardless of whether either testing strategy is proven to be superior. Thus, the precision of the estimated difference in outcomes between the 2 arms of the trial (i.e., width of the confidence interval [CI]) has been considered in addition to the statistical power for the hypothesis tests.

Based on the distribution of coronary disease expected in this patient population (approximately 15% obstructive disease [i.e., greater than or equal to 50% stenosis of the left main coronary artery or greater than or equal to 70% stenosis of 1 or more of the other major epicardial coronary arteries], 40% nonobstructive disease, and 45% normal coronary arteries) and based on national claims data or published information from other databases, the event rate at 2.5 years (the average length of follow-up in PROMISE) for the primary composite endpoint in subjects randomized to the functional testing strategy was projected to be approximately 9%.

With this event-rate projection in the functional testing arm, a key driver of the sample size is the magnitude of benefit that can reasonably be expected to be achieved with the anatomic testing strategy. This determination requires careful consideration of multiple characteristics of CTA, including its likely incremental diagnostic and prognostic accuracy and its ability to more effectively detect nonobstructive CAD. A careful assessment of the impact of the advantages of CTA with respect to these test characteristics translates to a projection (hypothesis) that CTA will reduce the primary composite endpoint by 20% (from 9% to 7.2% at 2.5 years).

Based on the event rates for each arm discussed above, sample-size requirements were formulated to provide high power for detecting the postulated 20% relative risk reduction. Recognizing, however, that the actual event rates and the outcome differences between the 2 testing strategies in PROMISE may vary somewhat from these estimates, sample-size requirements were calculated for several different combinations of event rates, effect sizes, and power levels in order to examine the sensitivity of the sample size to different event rates and outcome scenarios that might conceivably arise in this trial.

Since the primary treatment comparisons in this study will be based on time-to-event methodology using the log-rank test or equivalently, the Cox proportional hazards model, the approach used for calculating sample-size requirements for PROMISE was based on the sample-size methodology for the proportional hazards regression model outlined in Schoenfeld.

To provide an adequate number of subjects for the trial that will be relatively robust in providing (1) excellent statistical power under various assumptions about the event rates in the functional testing arm and the magnitude of the benefit of anatomic testing compared with functional testing for reducing the primary endpoint, (2) adequate power

for selected secondary endpoints, (3) adequate power for assessing noninferiority in the event that superiority is not demonstrated, and (4) a relatively high degree of precision for estimating the true effect of an anatomic vs. functional testing strategy regardless of whether the final result has a *P* value that is statistically significant, the study will enroll 10,000 subjects (5,000 per arm). This number will provide greater than 90% power for detecting a 20% reduction in the primary clinical endpoint if the 2.5-year event rate in the functional testing arm is 8% or higher and 80% power if the event rate is as low as 6%. This number of patients will also provide adequate power for detecting a smaller (16%–17%) reduction if the event rate in the functional testing arm is 8% to 9% or higher and acceptable power for selected secondary endpoints, allowing for up to a 3% loss to follow-up. Ten thousand patients will also provide 90% power for testing noninferiority with a margin of 1.10 (expressed as a hazard ratio of CTA vs. functional testing) if the functional testing arm event rate is 9%, 86% power if the event rate is 8%, and 81% power if the event rate is 7%, assuming that anatomic testing is only better than functional testing by 10%, an assumption that was felt to be reasonable for the noninferiority assessment. That is, we will have excellent power for demonstrating that anatomic testing is not worse than functional testing by more than 10% under these various assumptions.

In summary, 10,000 patients will provide excellent and robust statistical power for assessing clinically relevant and realistic outcome differences between the 2 testing strategies being studied in this trial.

## **F2 Statistical Analysis Plan**

Statistical analysis will be performed at the PROMISE SDCC at DCRI. All major treatment comparisons between the randomized groups will be performed according to the principle of "intention-to-treat"; that is, subjects will be analyzed (and endpoints attributed) according to the diagnostic testing strategy to which subjects were randomized, regardless of subsequent additional testing or postrandomization treatment and medical care. Statistical comparisons will be performed using 2-sided significance tests. Additional perspective regarding the interpretation of the data will be provided through extensive use of CIs and graphical displays.

### **2.a Analysis for the Primary Endpoint**

The statistical comparison of the 2 randomized arms (anatomic vs. functional diagnostic testing) with respect to the primary composite endpoint (death, MI, major peri-procedural complications, or hospitalization for unstable angina) will be a "time-to event" analysis and therefore will be based on the time from randomization to the first occurrence of any of the components of the primary composite endpoint. The Cox proportional hazards model will be the primary analytic tool for assessing outcome differences between the 2 randomized arms. To appropriately account for heterogeneity among the subjects, the overall comparison will be adjusted for a selected set of prognostically important baseline covariates that will be carefully defined and prespecified in the statistical analysis plan. The level of significance for the assessment of the primary endpoint will be  $\alpha=0.05$ .

In addition to the statistical hypothesis testing, Kaplan-Meier "survival" (or event-free) estimates will be calculated for each randomized arm as a function of follow-up time to display the event rates graphically. A hazard ratio and 95% CI for descriptively

---

summarizing the difference in outcome between the 2 study arms will be computed using the Cox model.

If the data provide evidence of an overall difference in outcome between the randomized arms, an assessment will be made of whether the effect is similar for all patients or whether it varies according to specific patient characteristics. In particular, this analysis will focus on whether the relative benefit differs according to subject age, sex, race, comorbidity, selected risk factors, characteristics of the precipitating symptoms, and the prerandomization specification of the functional test that would be used if the subject was randomized to the functional testing arm. This latter factor is built into the randomization scheme. For subjects for whom the prerandomization choice for functional testing (if the subject was assigned to the functional testing arm) was stress nuclear imaging (for example), the outcomes of these subjects in the CTA arm will be compared to the outcomes of corresponding subjects randomized to functional testing. In this way, CTA can be compared with stress nuclear imaging, as well as with each of the other functional testing modalities with the benefits of randomization in each comparison maintained by virtue of the stratified randomization scheme. These analyses will utilize the Cox model by testing for interactions between the randomized testing strategy and these specific baseline variables. In addition to the formal assessment of testing strategy by covariate interactions, effects of the diagnostic testing strategy characterized by a hazard ratio and 95% CI will be calculated and displayed for prospectively defined subgroups of subjects defined by the variables listed above. These descriptive hazard ratios will be carefully interpreted in conjunction with the formal interaction tests.

If the data do not provide statistical evidence that the CTA testing strategy is superior to functional testing with respect to the primary endpoint, a test for noninferiority of the anatomic testing strategy will be performed. This assessment will be based on a noninferiority margin of 1.10 (expressed as a hazard ratio for CTA vs. functional testing). The noninferiority assessment will be performed by comparing the upper limit of the 95% CI for the hazard ratio with the noninferiority margin. If the upper limit of the CI falls below 1.10, noninferiority will have been demonstrated. We emphasize that the superiority hypothesis will be assessed first, and if significant, the noninferiority assessment will not be performed. Only if superiority is not demonstrated will the noninferiority analysis then be performed.

## **2.b Analysis of Secondary Endpoints**

Secondary endpoints that will be evaluated include (1) a composite endpoint consisting of death, MI, or hospitalization for unstable angina; (2) death or MI; (3) major periprocedural complications (stroke, major bleeding, renal failure, anaphylaxis); (4) a composite of the primary endpoint or invasive catheterization without obstructive CAD, (5) invasive catheterization without obstructive CAD, (6) resource-use patterns, medical care costs and incremental cost effectiveness; and (7) QOL. In addition, major adverse cardiac events (events other than the endpoints listed above) will be monitored and reported.

The analysis of secondary endpoints 1 through 4 will be similar to that outlined for the superiority assessment of the primary endpoint, using time from randomization until the first occurrence of any component of the specific secondary endpoint (or censoring) as the response variable, and assessing group differences using the Cox proportional hazards model. The effect of the diagnostic testing strategy on these secondary clinical endpoints will be descriptively summarized using hazard ratios (with associated CIs)

---

computed from the Cox model. Kaplan-Meier curves will be computed to graphically display the cumulative event rates of the 2 randomized arms as a function of time from randomization. We note that the analysis of secondary endpoint (3) above (major peri-procedural complications) will have to be interpreted cautiously, particularly if there should be a higher death rate in one arm compared with the other. To deal with this complexity and clarify and enhance the interpretation of this comparison, the analysis of this endpoint will be supplemented with further analyses by considering major peri-procedural complications and death as a combined endpoint.

Plans for the analysis of the QOL and economic endpoints are addressed below in Sections F2.g and F2.h.

## **2.c Analysis of Diagnostic Testing Core Data**

The DTCC will implement robust QA programs to ensure uniformity and high-quality testing in support of the primary aims of PROMISE.

Two important components of information from the diagnostic test QA activity will be analyzed by the SDCC. The DTCC will review the first 8000 subjects' initial diagnostic test for technical quality, and each test will be assigned a quality assessment using an ordinal categorical scale (for example, excellent, good, fair, poor, uninterpretable). Using simple frequency counts, the SDCC will tabulate a description of the distribution of this scale on an ongoing basis by type of test and by testing site in order to provide feedback to the sites on their performance, to inform the study leadership and the DSMB as to the quality of the diagnostic testing, and to flag potential problem areas, whether by testing site or across a given testing modality, for remedial attention. This quality measure will be compared among the different testing modalities using rank-based tests (e.g., Kruskal-Wallis nonparametric analysis of variance) and ordinal logistic regression to characterize, describe, and assess any differences in overall quality among the various testing modalities. In particular, the technical quality of the anatomic (CTA) tests will be compared with the quality of the functional tests. This comparison may be helpful in interpreting the comparisons of the 2 randomized arms with respect to the clinical outcomes.

The second important component of information from the diagnostic test QA activity is the quality of test interpretations. Approximately 10% of tests will be overread by the DTCC using a categorical level of coronary disease risk. The site interpretation of level of risk will be compared with the level of risk using the same scale assessed by the core lab's overread of the test, and overall summary statistics of the agreement between the site and core lab assessments will be computed. Raw proportions of agreement (perfect agreement, and agreement differing by less than or equal to 1 category of risk) will be tabulated, and Kappa statistics will be used to characterize the level of agreement. The Kappa statistics are "chance corrected" (i.e., adjusted for agreement due to chance), and both unweighted and weighted Kappa statistics will be used in these analyses since more substantial disagreements in the assessment of risk for a given subject would be more serious than small disagreements. These agreement statistics will then be compared across the different testing modalities to determine whether the level of agreement between the site readings and the core lab readings varies with the type of test.

Another important component of information to characterize data quality for the secondary endpoints that involve non-obstructive CAD will be the review of selected

---

coronary angiograms to determine the degree to which site-reported assessments of non-obstructive coronary disease are concordant with carefully-performed core lab QCA. The same type of agreement statistics as described above, including raw proportions of agreement and chance-corrected Kappa statistics, will be used to describe and characterize the accuracy of the site-reported assessments of non-obstructive CAD.

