## 2.d Subject Recruitment Plans and Consent Process

Diagnostic testing for the assessment of CAD symptoms is ordered by physicians of all specialties; is performed in multiple settings, including physician offices, hospital outpatient departments, and diagnostic testing facilities; and is interpreted by physicians of multiple specialties, including primary care physicians, cardiologists, and radiologists. Therefore, subjects will be recruited from multiple clinical settings, including outpatient

clinics, urgent care centers, and testing facilities. Sites that do not perform the full range of diagnostic testing, including CTA, will be paired with regional referral centers for echo, nuclear, and/or CTA testing where subjects may undergo the necessary testing. Existing clinical referral and research networks will be used to identify and enroll subjects.

Subjects will be recruited from 200 to 250 clinical sites. All potential PROMISE sites will obtain IRB/Institutional Ethics Committee (IEC) approval of the protocol and the associated consent form and any recruitment tools. Written informed consent will be obtained from each subject before to any study procedures are performed. Assessment of CAD risk will begin during screening to ensure eligibility. It will include medical history and physical exam and laboratory testing for the presence/absence of major cardiac risk factors, including BP/hypertension, diabetes, cholesterol (low-density lipoprotein [LDL], high-density lipoprotein [HDL]), smoking, family history, sedentary life style, obesity, cerebrovascular and PAD history, and ABI.

Subjects will be identified and enrolled in a step-wise process as follows:

1. All subjects being considered for outpatient noninvasive testing for the initial evaluation of symptoms suspicious for clinically significant obstructive CAD will be screened.
2. Subjects meeting inclusion criteria and not having any of the exclusion criteria will be approached to participate in the study and have the study explained to them.
3. Subjects agreeing to participate after having all their questions answered will be asked to document their agreement on the study-specific IRB-approved consent form with a signature.

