## **2.e Subject Randomization**

Eligible subjects who have given written informed consent and meet all inclusion and no exclusion criteria will be randomly assigned in equal proportions (1:1) to either the anatomic or functional diagnostic testing arm of the trial. A computer-generated permuted block randomization schedule with stratification by clinical site will be used in the trial. Before randomization, the managing caregiver, site investigator, or authorized designee will be asked to indicate the functional test he or she would plan to use if the subject were randomized to the functional testing arm. This information will be tracked and used as another stratification factor in the randomization scheme to facilitate comparisons of anatomic vs. functional testing according to the type of functional test. Subject randomization will be accomplished by telephone through a centralized toll-free interactive voice response system (IVRS).

If a subject is randomized but does not undergo the planned initial diagnostic test within 30 days of randomization, that subject will still be followed and included in the intention-to-treat statistical comparisons according to his or her randomized treatment assignment.

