### **3.c Functional and Anatomic Testing and Cardiac Catheterization**

#### ***Equipment and Protocols***

Criteria for qualification of participating sites or referral laboratories will include use of standard equipment for usual-care testing (stress echo, stress nuclear, and exercise ECG) as defined in current practice guidelines, and greater than or equal to 64-slice MDCT technology for coronary CTA. Similarly, all test acquisition protocols will adhere to best-practice standards as defined in current national practice guidelines.

 Sites will be allowed to use their own standard acquisition protocols as long as they

---

fall within the standard-of-care guidelines. Sample protocols are provided in the Manual of Operations and Procedures (MOP).

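### The between-modality comparison of test quality makes no allowance for clustering by testing laboratory or for local choice of functional test; the size of the error depends on an intraclass correlation the documents do not give

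*Supplement*

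**What the plan says.** Protocol Amendment 2, F2 2.c (Analysis of Diagnostic Testing Core Data) states: "The DTCC will review the first 8000 subjects' initial diagnostic test for technical quality". Each test receives an ordinal grade; the section offers a five-category scale as an example. It continues: "This quality measure will be compared among the different testing modalities using rank-based tests (e.g., Kruskal-Wallis nonparametric analysis of variance", and names ordinal logistic regression alongside. CTA against the functional tests is singled out, with the purpose: "This comparison may be helpful in interpreting the comparisons of the 2 randomized arms with respect to the clinical outcomes". Testing site enters only through frequency tables used for feedback and for flagging problems. The SAP does not carry this comparison, and its Section 6 (General Methodology) has no provision for clustering.

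Other parts of Amendment 2 describe where the tests come from:

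- D2 2.d: "Subjects will be recruited from 200 to 250 clinical sites". Sites without the full range of tests "will be paired with regional referral centers for echo, nuclear, and/or CTA testing where subjects may undergo the necessary testing".
- D3 3.c (Equipment and Protocols): "Sites will be allowed to use their own standard acquisition protocols as long as they" stay within standard-of-care guidelines.
- A1 (Study Design): the care team selects the functional test.
- D2 2.e: "A computer-generated permuted block randomization schedule with stratification by clinical site will be used in the trial", with the intended functional test as a second stratification factor.

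**The concern.** Grades from one laboratory share equipment, an acquisition protocol and staff, so they are likely to be correlated. In standard form, both named methods treat the grades as independent. There are two routes to understated standard errors:

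- Quality may vary by laboratory and modality together. For example, a site's CTA scans may be done at a referral centre and its stress tests in house.
- A quality effect may be common to everything done at a site while sites differ in which functional test they favour. Functional modality then becomes partly a site-level factor.

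The protocol means this comparison to help interpret the clinical result. An understated p-value could turn ordinary variation between laboratories into an apparent quality advantage of one modality, and so into an explanation for the trial's finding.

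**Working it through.** The plan states no sample size, power, alpha or ICC for this comparison, so there is no figure of its own to reproduce.

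**Inputs from the documents.** 8000 graded tests (F2 2.c); 200–250 sites, about 220 in the synopsis; 1:1 allocation within site (D2 2.e); functional mix of nuclear 61%, echo 18%, exercise ECG 21% (claims data in C5, used as a proxy); two-sided tests (F2).

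**Assumptions.** Nominal level 5%; five-level grade; ICC 0.01 to 0.10 on the latent scale; coefficient of variation (CV) of site size 0 or 1; functional choice ranging from the same mix at every site to a single functional test per site. Sites stand in for laboratories. A referral centre serving several sites would make the real clusters larger.

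**Design effect.** Tests per site: 8000/220 = 36.4, so about m = 18.2 per arm. DE = 1 + ((1 + CV²)m − 1) × ICC, and actual alpha = 2(1 − Φ(1.96/√DE)).

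- ICC 0.05, CV 0: DE = 1 + 17.2 × 0.05 = 1.86; 1.96/√1.86 = 1.44; alpha about 15%.
- ICC 0.05, CV 1: DE = 1 + 35.4 × 0.05 = 2.77; 1.96/√2.77 = 1.18; alpha about 24%.
- ICC 0.01: DE = 1.17 to 1.35; alpha about 7–9%.

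This applies to two groups whose laboratory effects are unrelated. The other cases need simulation.

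**Simulation with no true modality difference** (220 sites, CV 1, 400–500 replicates per cell; Monte Carlo error about 1 point at 5% and at most 2.5 points). Rejection rates of the unadjusted rank test:

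| Comparison and structure | ICC 0.01 | ICC 0.05 | ICC 0.10 |
|---|---|---|---|
| Four modalities, laboratory-by-modality effects | 7–11% | 17–37% | 32–52% |
| Four modalities, shared site effect, choice partly concentrated | 7% | 13% | 17% |
| Four modalities, shared site effect, one functional test per site | 11% | 27% | 40% |
| Four modalities, shared site effect, same mix everywhere | 3–5% | 3–5% | 3–5% |
| CTA vs functional, shared site effect | 3–7% | 3–7% | 3–7% |
| CTA vs functional, laboratory-by-modality effects | 6–9% | 17–24% | 29–31% |

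Ranges in the laboratory-by-modality rows run from the same mix everywhere to one functional test per site. With equal site sizes, ICC 0.05, partly concentrated choice and 200 or 250 sites, the four-modality rate is 16–17% (laboratory-by-modality) or 7–8% (shared).

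**Does the named regression help?** At ICC 0.05 the ordinary ordinal logistic likelihood-ratio test reached the same decision as Kruskal-Wallis in all 120 data sets checked. Naming the regression without a clustering provision changes nothing.

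**Does allowing for clusters help?** A site-clustered sandwich variance applied to the ranks gave 4–9% for four modalities and 3–8% for CTA versus functional across all scenarios. The high end arises with one functional test per site, where echo and exercise ECG sit in only about 0.18 × 220 = 40 and 0.21 × 220 = 46 sites. It appears there even at ICC 0 (9%), so it is a small-sample feature of the sandwich variance, not clustering left unaccounted for.

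**The case against.** A reader might infer that false modality differences will certainly appear far more often than 5%. The documents do not support that: they give no ICC, no site-level modality mix and no alpha for this comparison (0.05 is set only for the primary endpoint). At ICC 0.01 the excess is a few points at most, and in one plausible structure there is none.

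A reader might also infer that the contrast between the randomized arms is undermined whenever laboratories differ. It is not. Allocation is 1:1 within site, so any effect common to a site balances. Local choice of functional test biases inference among the functional tests, not CTA against all of them. What remains is laboratory-by-modality variation, which the referral arrangement makes possible but does not establish.

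Other points against are fair:

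- Kruskal-Wallis is given as an example, and ordinal logistic regression could carry a laboratory term. That the tests are treated as independent is read from silence.
- D3 3.a and 3.e require sites to qualify in every modality, D3 3.e has centrally trained technicians assess the studies, and D3 provides for retraining of poor sites. All of this should reduce variation between laboratories. Yet the protocol still tabulates quality by testing site to find problem areas, so it expects some to remain.
- This is supportive quality assurance. SAP Section 18 fixes the order of interpretation without it and treats all other analyses as ancillary.

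These points narrow the claim. They do not supply the missing provision.

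**Conclusion.** The gap is real but minor. F2 2.c names methods whose standard form ignores clustering, in a setting where the protocol's own arrangements make clustering likely, and nothing in the SAP mends it. The consequence is conditional. At ICC 0.05 with unequal sites, a nominal 5% four-modality test would reject in about 17–37% if quality varies by laboratory and modality, and in 13–27% if the site effect is shared but functional choice is concentrated. At ICC 0.01 both ranges are about 7–11%. CTA versus functional is at risk only if laboratory effects differ by modality (17–24% at ICC 0.05). All of this rests on the assumed ICC, five-level grade, site-size variation and functional mix.

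No primary or secondary endpoint test uses the quality grade, so none is affected. The exposure is to a misleading side explanation of the trial result.

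**What to change.** In F2 2.c, or in the SAP if the comparison is moved there:

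- Take p-values and confidence intervals from an ordinal logistic model with modality as the factor and testing laboratory accounted for. Use either a cluster-robust variance with a small-sample correction, or random effects for laboratory and laboratory-by-modality.
- For CTA versus functional, specify a within-site contrast. Conditioning on site removes only the shared effect, so the variance must still allow for laboratory-by-modality differences.
- Keep Kruskal-Wallis and the other rank-based results as description.

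Testing site is already recorded for the planned tabulations, so the cost is a few lines of text and some analysis code. The real price is wider intervals for differences in quality between modalities.

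A cluster bootstrap for the agreement statistics in the same section is optional. About 10% of 10,000 tests overread is roughly 1000, or 4–5 per site over 200–250 sites, which at ICC 0.05 gives a design effect of only 1 + 3 × 0.05 = 1.15 to 1 + 4 × 0.05 = 1.20.
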